### Sample Size

The primary objectives of ITIP3 are to describe the clinical outcomes of children who meet the inclusion criteria for ITIP3 and to investigate whether the percentages of children cured on day 14 among those with either fast breathing or chest indrawing pneumonia and comorbidities such as severe malaria, anemia, severe acute malnutrition, or HIV are lower than those without these comorbidities in the standard of care groups in the concurrent clinical trials. For hypothesis testing, we focused on four high-frequency and high-mortality comorbidities (ie, severe malaria, anemia, severe acute malnutrition, and HIV infection or exposure) within ITIP3. We estimate that the study can enroll 1000 children during the time it is concurrently conducted with the ITIP1 and ITIP2 clinical trials, and we estimate the effect sizes for the primary outcome comparisons for which we have 80% power. We also assume that 1000 children can be enrolled in each of the standard care groups in ITIP1 and ITIP2. With available data from KCH and Malawi, we estimate the prevalence of severe pneumonia to be 10%-24%, severe malaria to be 15%-20%, severe acute malnutrition to be 4%-7%, and HIV seropositivity to be 5%-10%. Based on the estimated treatment failure rates for ITIP1 and ITIP2, we conservatively estimate that clinical cure will be observed in 90%-95% of children in ITIP1 and 85%-90% in ITIP2. We estimate the effect sizes we would be able to see for various comparisons between ITIP3 and ITIP1 or ITIP2, along with different estimated prevalence rates (Table 1). For example, comparing the clinical cure among children with HIV infection or exposure in ITIP3 and those in the standard of care group in ITIP2, if the prevalence of HIV infection or exposure is 10% in ITIP3, we will have 80% power to detect an absolute difference in proportions of 9.9% if at least 90% of the children in ITIP2 are cured and 80.1% of the children with HIV infection or exposure in ITIP3 are cured. Note that the absolute observable difference is largest for severe acute malnutrition, as that outcome is expected to have the lowest prevalence among the outcomes of interest. Nonetheless, we considered all the estimated effect sizes to be clinically relevant.

**Table 1 table1:** Observable effect sizes for comparisons of Innovative Treatments in Pneumonia (ITIP) 3^a^ with ITIP1^b^ or ITIP2^c,d^. N (ITIP1 or ITIP2) = 1000.

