**Severe acute malnutrition**						
	**7%**					
		70	9.1	95	85.9
		70	11.7	90	78.3
		70	13.5	85	71.5
	**4%**					
		40	12.2	95	82.8
		40	15.6	90	74.4
		40	17.8	85	67.2

^a^Prospective observational study.

^b^Randomized controlled clinical trial evaluating the optimal duration of treatment with amoxicillin for fast breathing pneumonia.

^c^Alpha value set to 5% and power set to 80%.

^d^Randomized controlled clinical trial evaluating the optimal duration of treatment with amoxicillin for chest indrawing pneumonia.

^e^Assuming similar values for fast breathing pneumonia and chest indrawing pneumonia to be able to compare the ITIP1 and ITIP2 cohorts.

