### Statistical Analysis

Generalized linear models with robust standard error will be used to compare the percentages (absolute risk differences) of children who are clinically cured by day 14 among ITIP3 children who have severe malaria (or are anemic or present with severe acute malnutrition, or are HIV positive or exposed) and children in the standard care groups in ITIP1 or ITIP2. Two-sided tests will be performed, with an alpha value of 0.05. No adjustments will be made for multiple comparisons because of the observational and exploratory nature of this study. If loss to follow-up is higher than 5%, multiple imputations will be considered for sensitivity analyses. The imputations will be performed separately for each cohort using multiple (n=20) hot deck imputations and the child’s age and gender and educational status of the caregiver. Multiple imputation estimates will be combined using the approach by Rubin [8]. Similar linear or generalized linear models will be used for secondary outcome analyses. Where appropriate, we will adjust for gender, age, weight, mid-upper arm circumference, HIV status, malaria, and vaccination status.

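### The 5% trigger for a missing-outcome analysis is set without regard to the comorbidity contrasts, and neither it nor the planned hot deck would reveal loss related to cure

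*Protocol article*

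**What the plan says.** Protocol article, Statistical Analysis: "If loss to follow-up is higher than 5%, multiple imputations will be considered for sensitivity analyses". The next sentence gives the method: "The imputations will be performed separately for each cohort using multiple (n=20) hot deck imputations", with the child's age and gender and the caregiver's education as the variables used. The section does not say whether the 5% is counted overall, per cohort or per comorbidity group.

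The primary contrasts are absolute differences in day 14 cure. Each of four comorbidity groups within ITIP3 is compared with the standard care group of ITIP1 or ITIP2. On expected cure, the Sample Size section says: "we conservatively estimate that clinical cure will be observed in 90%-95% of children in ITIP1 and 85%-90% in ITIP2". Table 1 gives group sizes of 40 to 200 in ITIP3 against 1000 comparators, with detectable differences from 5.5 to 17.8 points.

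Limitations and Bias names loss to follow-up as a possible source of bias and lists reminders, stipends and home visits to limit it. It also promises sensitivity analyses in general terms, in connection with differences between the three study protocols.

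**The concern.** A fixed percentage is a sensible cut-off only if losses below it cannot matter for the comparison. Here the outcome of interest, non-cure, is expected in a small share of children, and the smallest difference the study is sized for is 5.5 points. Five percent missing is not negligible on that scale if lost children fare differently from those seen.

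Two features add to this. The trigger has no stated denominator, while each primary contrast rests on a comorbidity group of 40 to 200 children. A group could therefore lose well over 5% while the cohort as a whole stays under it. Also, the planned imputation draws outcomes from children alike in age, gender and caregiver education. If children within such a class are lost because they did badly, the imputed values will look like those of the children who returned. The check is then weak even when it is run.

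At stake is whether a reader can tell how far each reported difference depends on children whose day 14 outcome is unknown.

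**Working it through.** **Inputs.** Comparator cure is 90%-95% in ITIP1 and 85%-90% in ITIP2 (Sample Size). ITIP3 group sizes, cure and detectable differences come from Table 1. Table 1 footnote: "Alpha value set to 5% and power set to 80" percent; Statistical Analysis: "Two-sided tests will be performed, with an alpha value of 0.05". Comparator size: "We also assume that 1000 children can be enrolled in each of the standard care groups in ITIP1 and ITIP2". The loss fraction is d = 0.05, the largest that does not exceed the trigger.

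**Reproducing the plan's figures.** I used a pooled-variance normal approximation, two-sided alpha 0.05, no continuity correction, and solved for 80% power:
- n=100 v 1000 at 90%: 9.86 points (plan: 9.9, the worked example in Sample Size).
- n=200 v 1000 at 95%: 5.50 points (plan: 5.5).
- n=40 v 1000 at 85%: 17.81 points (plan: 17.8).

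**The trigger against expected non-cure.**
- ITIP1 at 95% cure: non-cure 5%, so 5/5 = 100%.
- ITIP1 or ITIP2 at 90%: 5/10 = 50%.
- ITIP2 at 85%: 5/15 = 33%.
- ITIP3 groups, non-cure 10.5% to 32.8%: 5/10.5 = 48% down to 5/32.8 = 15%.

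**Worst-case shift at 5% loss.** Let p be cure among children seen. If every lost child in a group is not cured, that group's cure is (1 − d)p, a fall of d × p. If every lost child is cured, it rises by d × (1 − p).

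| Contrast | Fall if all lost ITIP3 children are not cured | Detectable difference | Share |
|---|---|---|---|
| Severe malaria, n=200, 89.5% v 95% | 0.05 × 89.5 = 4.5 | 5.5 | 81% |
| Malnutrition, n=40, 82.8% v 95% | 0.05 × 82.8 = 4.1 | 12.2 | 34% |
| Malnutrition, n=40, 67.2% v 85% | 0.05 × 67.2 = 3.4 | 17.8 | 19% |

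If only the comparator is affected, the fall is 0.05 × 85 = 4.25 to 0.05 × 95 = 4.75. The one-group bound is therefore 3.4 to 4.75 points. Over the 24 rows of Table 1, the ITIP3-side shift exceeds half the detectable difference in 6: severe malaria at n=200 and n=150 against 95% and 90%, and anemia and HIV at n=100 against 95%.

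For severe malaria at 89.5% v 95%, opposite extremes in both groups give:
- Smallest difference: 0.95 × 95 − (0.95 × 89.5 + 5) = 90.25 − 90.025 = 0.2 points.
- Largest difference: (0.95 × 95 + 5) − 0.95 × 89.5 = 95.25 − 85.025 = 10.2 points.

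**Less extreme loss.** If lost ITIP3 children fail at k times the observed non-cure q, the shift is d × (k − 1) × q:
- k=2: 0.05 × 10.5 = 0.5 to 0.05 × 32.8 = 1.6 points.
- k=3: 0.05 × 2 × 10.5 = 1.1 to 0.05 × 2 × 32.8 = 3.3 points.

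If all lost children in both groups are not cured, the shift is 0.05 × (difference), which is 0.3 to 0.9 points.

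**Illustration (assumed counts, pooled z-test).** Comparator 950/1000, fully observed. Severe malaria: 200 enrolled, 10 lost (exactly 5%), 175/190 cured. The complete-case difference is 95.0 − 92.1 = 2.9 points, p = 0.11. If 3 of the 10 were not cured, cure is 182/200 = 91.0%, the difference is 4.0 points and p = 0.03. That is 30% non-cure among the lost against 15/190 = 7.9% among those seen, or 3.8 times.

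**Denominator (assumption).** If the 5% is counted over all of ITIP3, up to 50 of 1000 may be lost without exceeding it. Suppose 4 of 40 malnourished children are among them (10%) and none is cured. That group's cure then falls by 0.10 × 82.8 = 8.3 points.

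**The case against.** The case against is substantial and much of it stands.

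- **Size.** The 3.4 to 4.75 points require every lost child in one group to be a failure. At two to three times the observed rate the shift is 0.5 to 3.3 points, and parallel losses in both groups nearly cancel. This stands; the larger figures are bounds, not expected bias.
- **Event rate.** A reader might infer that 5% loss is as large as the whole non-cure rate being compared. The documents support that only for ITIP1 at 95% cure.
- **Direction.** Losing exposed children who failed makes the complete-case difference too small, which works against the hypothesis of lower cure with comorbidity. Creating a false difference needs mainly failures among lost comparators or mainly cures among lost ITIP3 children. This stands, but hiding a real difference is also an error.
- **Mitigation.** Missed visits prompt home visits, accepting one is an eligibility condition, and day 30 information is also sought. Losses may be few. That reduces the problem but does not show what the remaining losses do.
- **Silence.** A reader might infer that complete-case results are certain to go unexamined. The article does not say so: it promises sensitivity analyses in general terms, and the full protocol is not shown. Those analyses, however, are linked to differences between the protocols, and none is named for missing outcomes. The one rule the article does state is the 5% trigger, and that rule can be assessed.
- **Remedy.** Simply removing the trigger and always running the hot deck would not expose outcome-related loss. This is correct and shapes the fix below.

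**Conclusion.** The point holds as a cheap improvement to a stated rule. The trigger is poorly matched to the primary contrasts because it has no group denominator, leads only to an analysis that may be considered, and points to an imputation that cannot show the effect of loss related to cure.

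Its practical weight is concentrated in severe malaria against ITIP1 at 95% cure, where the one-group bound is 81% of the detectable difference. In 18 of the 24 Table 1 rows the ITIP3-side bound is no more than half of it. The documents therefore do not support saying that losses below the trigger can generally create or hide most of the difference sought.

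These figures assume cure rates as in Table 1, loss of exactly 5%, and outcome among the lost as specified for each scenario. The documents give no expected loss rate. The 8.3-point figure for malnutrition rests on the further assumptions that the 5% is counted over the whole ITIP3 cohort and that 4 of 40 are lost with none cured.

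**What to change.** Replace the 5% trigger and the conditional wording with a best/worst-case or tipping-point analysis of day 14 cure for every primary comorbidity contrast, whatever the loss. Report the number and percentage lost for each comorbidity group and each comparator group. Keep the 20-fold hot deck imputation as a supplementary analysis.

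This needs no new data, only a change of wording and a little more programming and reporting. The drawback is that the bounds will be wide for the smallest groups; a tipping-point presentation makes those easier to read than the extremes alone.

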### Limitations and Bias

A limitation to this study and a potential source of bias is loss to follow-up. To minimize loss to follow-up, caregivers are provided clear follow-up instructions as well as called the afternoon before their visits to remind them to visit the following day. A travel stipend for all follow-up visits is provided. In addition, children are followed up with home visits upon a missed visit. An additional limitation related to follow-up is that children in this observational study are followed up less frequently and have different assessment time points than those who are enrolled in the two clinical trials for fast breathing pneumonia and chest indrawing pneumonia. The three study protocols also have differences in the eligibility criteria and treatment regimens. These differences, in addition to the different follow-up schedules, will present some challenges for analyses and interpretation of results. Where possible, we will attempt to adjust for baseline characteristics (not in the causal pathway) as well as perform sensitivity analyses. Nevertheless, the potential for unmeasured confounders cannot necessarily be overcome or assessed. Other limitations to this study are the clinical diagnosis of pneumonia, rather than a microbiological or radiological diagnosis, and the limited follow-up duration of 30 days. All study staff receive rigorous training in the WHO IMCI classification of pneumonia; however, no microbiological or radiological tests are routinely undertaken unless clinically indicated. Of note, this was a pragmatic design decision, as in standard clinical care in this setting, microbiological or radiological tests are not typically undertaken unless clinically indicated. In addition, it is possible that we are missing longer-term consequences after treatment, given the limited follow-up period of 30 days.

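### The sensitivity hot deck for missing day 14 outcomes leaves out the comorbidities that define the ITIP3 contrasts and the last observed clinical status

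*Protocol article*

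**What the plan says.** All of the following comes from the protocol article.

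- **Trigger and role** (Statistical Analysis): "If loss to follow-up is higher than 5%, multiple imputations will be considered for sensitivity analyses".
- **Method** (same section): "The imputations will be performed separately for each cohort using multiple (n=20) hot deck imputations". Three variables are named for this step: how old the child is, the child's gender, and the caregiver's education. The 20 results are combined by Rubin's approach.
- **Contrast** (same section): the models are "to compare the percentages (absolute risk differences) of children who are clinically cured by day 14 among ITIP3 children who have severe malaria" (or anemia, severe acute malnutrition, or HIV infection or exposure) and children in standard care in ITIP1 or ITIP2.
- **Meaning of cohort**: footnote e of Table 1 uses the word for whole studies: "to be able to compare the ITIP1 and ITIP2 cohorts". The natural reading is therefore one donor pool for all of ITIP3, divided only by age, gender and caregiver education.
- **Why it matters to the authors** (Limitations and Bias): "A limitation to this study and a potential source of bias is loss to follow-up".

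**The concern.** An imputation model should contain the variables that define the analysis and those that best predict the missing outcome. The stated set contains neither.

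- **Comorbidity.** Each test compares one comorbidity group of ITIP3 with an outside group. Given age, gender and education, the imputed outcomes are unrelated to comorbidity, so part of the group's data is replaced by the ITIP3 cell average. The Introduction cites mortality odds ratios of 4.68 for HIV/AIDS and 4.27 for severe malnutrition, so the authors' own source treats these conditions as predictive of outcome.
- **Last observed status.** ITIP3 children are examined on day 6, and on day 2 if hospitalized (Study Procedures). A child who is not improving on day 6 and is then lost would be given the result of a child matched on three background variables only.

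At stake is the value of the one analysis named for checking missing outcomes. It could move the estimate away from the truth in a setting where the complete-case estimate is sound.

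**Working it through.** **Step 1. The plan's own figure.** Sample Size and Table 1 give 80% power for 90% against 80.1% cured, with 1000 comparator children and 100 with HIV infection or exposure. Table 1 states "Alpha value set to 5% and power set to 80"%; Statistical Analysis makes the tests two-sided.

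- Pooled cure = (900 + 80.1)/1100 = 0.891
- SE under the null = sqrt(0.891 x 0.109 x (1/1000 + 1/100)) = 0.0327
- SE under the alternative = sqrt(0.90 x 0.10/1000 + 0.801 x 0.199/100) = 0.0410
- z = (0.099 - 1.96 x 0.0327)/0.0410 = 0.85, so power = 80.3%

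The figure is reproduced. The same formula gives 80.0% for severe acute malnutrition at 4% (n=40, 90% against 74.4%). These two rows serve as the test cases.

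**Step 2. Bias formula.** Let m be the share with a missing day 14 outcome, the same in and outside the group and unrelated to outcome within each. Let G be cure in the comorbidity group, O cure in the other ITIP3 children, and w the group's share of ITIP3. The formula takes comorbidity to be unrelated to the matching cells.

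- ITIP3 cure: P = w x G + (1 - w) x O
- Expected group cure after the hot deck: (1 - m) x G + m x P
- Bias = m x (P - G)

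Under this missingness the complete-case estimate has expectation G, so its bias is zero.

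**Step 3. Numbers.** G and w come from Table 1. O and m are not in the document and are assumed: O = 85%-90%, m = 5%-10%.

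| Group | O | P | P - G (points) | Bias, m = 5% | Bias, m = 10% |
|---|---|---|---|---|---|
| HIV, w = 10%, G = 80.1% | 85% | 84.51% | 4.41 | +0.22 | +0.44 |
| HIV | 90% | 89.01% | 8.91 | +0.45 | +0.89 |
| HIV | 80.1% | 80.1% | 0 | 0 | 0 |
| HIV | 75% | 75.51% | -4.59 | -0.23 | -0.46 |
| Malnutrition, w = 4%, G = 74.4% | 85% | 84.58% | 10.18 | +0.51 | +1.02 |
| Malnutrition | 90% | 89.38% | 14.98 | +0.75 | +1.50 |

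In the HIV row with O = 90% and m = 10%, the 9.9-point difference becomes 9.01. The planning formula evaluated at 9.01 gives 74.2%. This is only a gauge of the shrinkage; it is not the power of the imputed analysis.

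**Step 4. Simulation of that row** (400 runs, 1000 children, 18 age/gender/education cells, 20 imputations). Bias in group cure, with Monte Carlo standard error:

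- hot deck as stated: +0.96 (0.19), against +0.89 by formula
- complete cases: +0.10 (0.21)
- hot deck with comorbidity added to the matching: +0.01 (0.23)

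**Step 5. Last observed status (every input assumed).** Suppose 25% of the HIV group is not improved at day 6 and 40% of these are later cured. Overall cure is still 80.1%, so the rest are cured in (0.801 - 0.25 x 0.40)/0.75 = 93.5%. Let 20% of the unimproved and 6.7% of the rest be lost.

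- Share observed = 0.25 x 0.80 + 0.75 x 0.933 = 0.900
- Complete-case cure = (0.200 x 0.40 + 0.700 x 0.935)/0.900 = 81.6%, bias about +1.5 points
- Hot deck with donors at 89.01% = 0.900 x 81.6% + 0.100 x 89.01% = 82.3%, bias about +2.2 points

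Here the stated hot deck adds to the error in the complete cases. Imputing given day 6 status would remove it, because loss in this example depends on that status alone.

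**The case against.** The other side has several good points.

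- **Small role.** Imputation is only to be considered, only above 5% loss, and only as a sensitivity analysis. Home visits, reminder calls and travel stipends are meant to keep loss low, so it may never be run. This stands. A reader might infer that the primary results are biased; the document does not support that.
- **Size and sign are assumed.** The document gives neither the missing share nor the cure rate of the other ITIP3 children. Those children are not healthy donors: each was enrolled for a qualifying condition, including severe respiratory distress and hypoxemia. This stands. A reader might reach 4 points by multiplying 20% missing by a 20-point gap, but nothing in the document supports either figure.
- **False reassurance is not established.** Raising group cure shrinks the difference the study hopes to show, so a difference that survives is not made less credible by this bias. This holds where the bias is upward; where other ITIP3 children do worse, the difference is exaggerated instead.
- **Detail may lie elsewhere.** The full protocol (Multimedia Appendix 1) is not shown and may add predictors. That would excuse silence, but the article is not silent: it fixes the method, the number of imputations, the stratification and the predictors.

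A reader might also infer that donors are drawn without a bootstrap, so that Rubin's variance is too small, or that known deaths would be imputed. The text does not say how donors are drawn, and it ties imputation to loss to follow-up. Neither is a finding.

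**Conclusion.** The point holds as a defect of a stated rule in a conditional sensitivity analysis. Followed as written, the hot deck pulls imputed group outcomes toward the ITIP3 average within age, gender and education cells. At 5%-10% missing, with other ITIP3 children assumed 85%-90% cured, the bias is about 0.2-0.9 points for HIV and 0.5-1.5 points for severe acute malnutrition, against the 9.9 and 15.6 points those two rows were planned to detect. With equal cure rates it vanishes; with other ITIP3 children at 75% it is -0.2 to -0.5 points for HIV. The figures assume missingness that is equal across groups and unrelated to outcome within them.

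The bias is modest. The reason to act is that the check can be further from the truth than the complete-case result it is meant to test. It deserves correction, but does not threaten the main analysis.

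**What to change.** Replace the list of imputation variables in Statistical Analysis.

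- **ITIP3:** keep age, gender and caregiver education; add indicators for the four comorbidities, pneumonia type, baseline severe respiratory distress and hypoxemia, and the last observed clinical status before day 14.
- **ITIP1 and ITIP2:** keep the three variables and add the last observed status available under each study's own schedule (days 2, 3 and 4 in ITIP1; days 2, 4 and 6 in ITIP2). ITIP1 has no day 6 visit, so a common day 6 predictor is not possible. The comorbidities and severity signs are grounds for exclusion from these trials, so they are not needed as predictors there.
- **Small groups:** some groups may hold only 40-100 children, too few for many donor cells. Use a regression-based imputation, or collapse cells under a rule set in advance.

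The cost is a sentence or two and a slightly more complex imputation model. No new data are needed: comorbidities and severity are assessed at screening, and clinical status at the scheduled visits.
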